#### Quality control

All acupuncturists and assessors will be required to undergo specialized training before the trial in order to guarantee consistent practices. The training program will include diagnosis, inclusion and exclusion criteria, the location of the acu-points, acupuncture manipulation techniques, and completion of the case report forms. Dropouts and withdrawals from the study will be recorded based on the intervention and follow-up periods. This trial will be monitored by the Scientific Research Department of Baoshan Hospital of Integrated Traditional Chinese Medicine and Western Medicine, Shanghai. A qualified clinical research investigator will be specified by the department office and periodic monitoring will guarantee accuracy and quality throughout the study.

### Withdrawal and dropout

All participants will have the right to withdraw from this study at any time. Participation will be terminated at any stage if the individual refuses to continue, withdraws consent, or violates the inclusion or exclusion criteria. The investigator may also exclude the participants from the study in order to protect their safety and/or if they are unwilling or unable to comply with the required study procedures after consultation with the institutional review board (IRB).

### Safety issues

Adverse events (AEs) will be recorded using the standard operating procedures for monitoring and reporting all AEs, which refer to all the harmful and unintended reactions that occur during the acupuncture treatment. The symptoms, date of occurrence, disappearance, causality, and severity of the AEs will be recorded. The putative AEs of acupuncture include the following: local bleeding or hematoma; more than slight sharp pain; aggravation of symptoms; syncope; nausea; headache; peripheral nerve injury; and infection. Participants will be informed of the potential AEs in advance.

During the study period, all researchers will ensure patient safety. When SAEs occur, the researchers will immediately halt the study and promptly provide appropriate management. The PI will also report the AEs to the IRB and halt the study partially or completely until further notice. Then, the IRB will determine whether the clinical study can be continued. The trial will be stopped if the IRB speculates unacceptable risks of SAEs. The hospital provides insurance coverage for harm associated with the interventions during this trial as necessary.

### Statistical methods

#### Sample size calculation

The enumeration data of parallel-controlled trial (1:1:1) are analyzed statistically using two-sided superiority test, where α = 0.05, power = 90%. The formula used for the calculation was as follows:$$ n\kern0.5em =\kern0.5em \frac{{\left({Z}_{1-a}+{Z}_{1-\upbeta}\right)}^2\kern0.5em \times \left({\sigma}_1^2+{\sigma}_2^2\right)}{\delta^2} $$

The change in the standard deviation of ECWM score before and after the treatment in the control group was presumed as 1 point and that in the treatment group as 3 points. This will be considered clinically significant if the change in the ECWM score before and after the treatment in the treatment group is 2 points higher than that in the control group, and the sample size was estimated as follows:$$ n\kern0.5em =\kern0.5em \frac{{\left({Z}_{1-a}+{Z}_{1-\upbeta}\right)}^2\kern0.5em \times \left({\sigma}_1^2+{\sigma}_2^2\right)}{\delta^2}\kern0.5em =\kern0.5em \frac{{\left(1.96+1.28\right)}^2\kern0.5em \times \left({1}^2+{3}^2\right)}{2^2}\kern0.5em =\kern0.5em 26 $$

Thus, a minimum of 27 patients was estimated in each group. The dropout rate is considered to be 20%; therefore, at least 33 patients should be enrolled in each group. Hence, a total of 99 patients are required to conduct this study.

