#### Statistical analysis

In this study, rather than the investigator, professionals will analyze the data using intention-to-treat and per-protocol approaches. The demographic and clinical characteristics of the participants (such as sex and age) will be processed based on descriptive analyses. The ECWM values and ESA scores will be compared as a baseline measurement. The quantitative data will be presented as average, standard deviation, median value, and range, while the qualitative data will be presented as the frequency and percentage.

For the primary and secondary outcome measurements, one-way ANOVA test will be applied to identify the differences between the of ECWM values and ESA scores among the groups. In case of abnormally distributed data, Kruskal–Wallis H test will be performed.

All AEs reported during the study will be included in the clinical report; then, the prevalence of AEs will be calculated. The percentage of participants with AEs in each group will be calculated and compared using the chi-squared or Fisher’s exact test. Statistical analyses will be performed using IBM SPSS Windows version 19.0 (IBM Co., Armonk, NY, USA). The tests were two-sided; a *P* value < 0.05 will be considered statistically significant.

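### The trial is sized for SDs of 1 and 3, but the tests named for the primary outcome (one-way ANOVA, or Kruskal–Wallis for non-normal data) do not allow for unequal spread

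*Protocol article*

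**What the plan says.** Under Sample size calculation, the protocol article plans for a two-sided 5% test with 90% power. It presumes that the SD of ECWM change "in the control group was presumed as 1 point and that in the treatment group as 3 points". It counts the result as clinically significant if the change "in the treatment group is 2 points higher than that in the control group". Both SDs enter the formula separately, as 1² + 3². The outcome is that "a minimum of 27 patients was estimated in each group" and, with 20% dropout, "at least 33 patients should be enrolled in each group", 99 in all.

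Under Statistical analysis, for both ECWM and eyelid strength, "one-way ANOVA test will be applied to identify the differences" among the groups. The one exception is this: "In case of abnormally distributed data, Kruskal–Wallis H test will be performed". Tests are two-sided at 0.05. The section names no unequal-variance form of the test, no pairwise procedure and no confidence interval.

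Under Primary outcome, the article promises group means and SDs of ECWM, and a comparison in mm between intervention and control groups.

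**The concern.** The sample size formula lets each arm have its own variance. One-way ANOVA, named without qualification, assumes one common variance. The trial is therefore powered under one model and tested under another. The fallback does not close the gap: its trigger is the shape of the distribution, and Kruskal–Wallis does not test equality of means when spreads differ.

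At stake is whether the primary test holds its stated 5% level if the planning SDs are right. Also at stake is whether later comparisons of Bi'nao with each control are calibrated if they reuse the ANOVA error term. The comparison with sham matters most, because the Background gives comparison with a placebo point as the reason for the trial.

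**Working it through.** **Inputs.** From Sample size calculation: SDs 1 (control) and 3 (treatment), difference 2, two-sided α 0.05, power 90%, 27 per arm before dropout and 33 after. From Randomization and blinding: allocation 1:1:1. Not given: the SD in the sham arm. It is assumed to be 1, with 2 and 3 as the range. The article's wording of the SD is loose; it is read here as the SD of the change, which is how the formula uses it.

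**The plan's own figure.** n = (1.96 + 1.28)² × (1² + 3²) / 2² = 10.4976 × 10 / 4 = 26.24, rounded up to 27. With dropout, 26.24 / 0.8 = 32.8, rounded up to 33, and 3 × 33 = 99. The stated sizes reproduce.

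**What pooling does to a contrast.** With equal n, the ANOVA error variance estimates (9 + s² + 1)/3, where s is the sham SD. Bi'nao versus sham needs (9 + s²)/2. Bi'nao versus no extra needling needs (9 + 1)/2 = 5. The square root of pooled over needed shows how far the standard error is off:

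| Sham SD | Pooled variance | Versus sham: needed, SE ratio | Versus no extra needling: needed, SE ratio |
|---|---|---|---|
| 1 | 3.67 | 5.0, 0.856 | 5.0, 0.856 |
| 2 | 4.67 | 6.5, 0.847 | 5.0, 0.966 |
| 3 | 6.33 | 9.0, 0.839 | 5.0, 1.125 |

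Against sham, the standard error is about 14% to 16% too small whatever the sham SD. Against no extra needling, the error changes sign.

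**Simulation under equal means.** 100,000 normal data sets per scenario, 27 per arm. The pooled contrasts are unadjusted and made regardless of the omnibus result; their rejection rate is 100% minus the interval coverage.

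| SDs (Bi'nao/sham/none) | ANOVA | Kruskal–Wallis | Pooled, versus sham: coverage (rejects) | Pooled, versus none: coverage (rejects) |
|---|---|---|---|---|
| 3/1/1 | 7.1% | 6.4% | 90.6% (9.4%) | 90.5% (9.5%) |
| 3/2/1 | 6.0% | 5.9% | 90.3% (9.7%) | 94.0% (6.0%) |
| 3/3/1 | 5.8% | 6.0% | 90.0% (10.0%) | 97.3% (2.7%) |
| all equal | 5.1% | 4.9% | – | – |

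Repeat runs at 3/1/1 gave 7.1% to 7.4% for ANOVA and 6.2% to 6.4% for Kruskal–Wallis. Results at 33 per arm are almost the same. At 3/1/1, Welch's ANOVA rejects 4.8% to 5.0%, and the Welch t-test for Bi'nao versus control rejects 4.9% (coverage 95.1%). An ordinary two-sample t-test on the two arms alone covers 94.8%. Sham versus no extra needling on the pooled error covers 99.96%, so it is heavily conservative.

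**Power.** SDs 3/1/1, means 2/0/0, 27 per arm: ANOVA 93%, Kruskal–Wallis 86%, Welch's ANOVA 84%, pooled-error contrast 94%, Welch contrast 89%. With all 33 per arm analysed, the Welch contrast has 94% and Welch's ANOVA 91%.

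**The case against.** The strongest reply is that the largest figures belong to a procedure the article does not contain. A reader might infer that its P values and confidence intervals for the Bi'nao comparisons are wrong. The documents do not support that, because no pairwise test or interval is stated, and a separate analysis plan may specify them. The 10% error and 90% coverage are conditional on ungated contrasts using the three-arm pooled error. A two-sample t-test at 1:1 is nearly exact. Contrasts made only after a significant omnibus test reject about 6.5% when all three means are equal. This stands, with one limit: the gate does not protect Bi'nao versus sham if both lie 2 points above no extra needling. The omnibus test is then almost always significant, and the gated contrast still rejects 9.7% (SDs 3/1/1).

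A second reply is that the SDs of 1 and 3 accompany a 2-point benefit. If Bi'nao does nothing different, all arms may share one distribution, and both tests then hold about 5%. This also stands. The inflation needs spread to differ while means do not, which is possible but which the protocol does not assert.

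Two other inferences go too far. Switching to a rank test does not lose the effect in mm, because the Primary outcome section reports means and SDs in mm whichever test is used. Nor can one say that the switch is likely to happen through a pile-up of recovered eyes at 0 mm, since the article gives no recovery rate.

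**Conclusion.** The mismatch is real and its size is modest. Neither named test is built for the unequal spread on which the sample size rests. If the SDs are as presumed and the means are equal, the omnibus ANOVA has a true level of about 7% with sham SD 1 and about 6% with sham SD 2 or 3. Kruskal–Wallis is at about 6% throughout.

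The larger risk is conditional. Ungated contrasts on the pooled three-arm error would reject about 10% for Bi'nao versus sham at every sham SD tried. For Bi'nao versus no extra needling they would run from about 10% (sham SD 1) to about 3% (sham SD 3), so even the direction of that error cannot be fixed from the article. All of this assumes normal data and reads the stated SDs as SDs of the change. It warrants a change of wording; it does not undermine the design.

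**What to change.** In Statistical analysis, name Bi'nao versus sham and Bi'nao versus no extra needling as Welch (unequal-variance) comparisons of ECWM change, each with a matching confidence interval in mm. If an omnibus test is kept, make it Welch's ANOVA. Keep the rank test as a sensitivity analysis, not as a replacement triggered by non-normality. The alternative is to justify a common SD and redo the sample size with it.

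The change is to wording only. The price is apparent power, at 27 per arm with SDs 3/1/1 and an unadjusted two-sided 5% level. A Welch contrast has about 89%, against about 94% with the pooled error. Welch's ANOVA has about 84%, against 93% for classical ANOVA. The Welch contrasts therefore stay closest to the stated 90%.

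The 89% needs a comparator SD of 1. If the sham SD were 3, the protocol's own formula would give 10.4976 × (9 + 9) / 4 = 47.2 per arm for Bi'nao versus sham, and the Welch contrast would have about 76% power even with all 33 per arm. The revised text should therefore also state the SD assumed for the sham arm.

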#### Statistical analysis

In this study, rather than the investigator, professionals will analyze the data using intention-to-treat and per-protocol approaches. The demographic and clinical characteristics of the participants (such as sex and age) will be processed based on descriptive analyses. The ECWM values and ESA scores will be compared as a baseline measurement. The quantitative data will be presented as average, standard deviation, median value, and range, while the qualitative data will be presented as the frequency and percentage.

For the primary and secondary outcome measurements, one-way ANOVA test will be applied to identify the differences between the of ECWM values and ESA scores among the groups. In case of abnormally distributed data, Kruskal–Wallis H test will be performed.

All AEs reported during the study will be included in the clinical report; then, the prevalence of AEs will be calculated. The percentage of participants with AEs in each group will be calculated and compared using the chi-squared or Fisher’s exact test. Statistical analyses will be performed using IBM SPSS Windows version 19.0 (IBM Co., Armonk, NY, USA). The tests were two-sided; a *P* value < 0.05 will be considered statistically significant.

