## Background

Bell’s palsy is a type of self-limited peripheral neuropathy with uncertain pathogens. Patients with Bell’s palsy suffer from dysfunction of the facial nerve and inflexible muscle movements; the majority of them will recover within 1–3 months. However, a few of them will undergo a long recovery procedure and/or leave some sequelae such as deviation of mouth angle, hemifacial spasm, or hypophasis [1, 2].

Hypophasis is frequently observed among some patients with Bell’s palsy, who are almost at complete recovery, and is occasionally accompanied with a tiny droopy corner of the mouth, which is the major obstacle before full recovery from Bell’s palsy, as well as posing huge difficulties for doctors or rehabilitation physicians. The syndrome of hypophasis will continue to maintain the status quo unless appropriate therapy is applied; however, over-treatment such as excessive exercise or transcutaneous electrical nerve stimulation may lead to facial spasm [3, 4].

Acupuncture therapy has been widely used for the treatment of Bell’s palsy in China and worldwide [5–8]. Although the efficacy of the therapy has not been sufficiently proved by systematic reviews [9], its application has been considered a reasonable resolution for the management of some symptoms such as hypophasis. Although acu-points around the eye socket are frequently selected in the approach of acupuncture therapy, high-efficiency widely accepted acu-points have not yet been reported.

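### The primary analysis takes no covariate although baseline ECWM is recorded for everyone, and the protocol leaves unclear whether end values or changes are compared

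*Protocol article*

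**What the plan says.** Four parts of the protocol article bear on this.

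- **Study setting.** ECWM and ESA are measured at allocation in all participants, and the first value is kept as baseline.
- **Primary outcome.** Group means and standard deviations of ECWM are to be calculated, and differences in eye crack width are to be compared, intervention against control. The wording can mean before–after differences or differences between arms.
- **Sample size calculation.** The trial is sized on change. The standard deviation of the change "in the control group was presumed as 1 point and that in the treatment group as 3 points", and the effect counts as clinically significant "if the change in the ECWM score before and after the treatment in the treatment group is 2 points higher" than in the control group.
- **Statistical analysis.** On baseline: "The ECWM values and ESA scores will be compared as a baseline measurement". On the primary and secondary outcomes: "one-way ANOVA test will be applied to identify the differences between the of ECWM values and ESA scores among the groups", with Kruskal–Wallis if the data are not normally distributed. A word seems to be missing before "of" in that sentence. No covariate is named for either method.

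Randomization and blinding describes block randomisation and mentions no stratification by baseline ECWM.

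**The concern.** A baseline reading of the primary outcome is usually the strongest single predictor of its later value. Here it is recorded for everyone, but the stated test cannot use it as a covariate. Two things are at stake.

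First, precision. Whatever part of the month-1 spread baseline explains stays in the standard error, and chance imbalance between small arms is left in the estimate (end values) or over-corrected (change scores).

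Second, the analysed quantity. The sample size depends on the variance of change. If the ANOVA is run on end values, the planned number rests on a different variance from the one that will govern the test. The protocol's wording does not settle which is meant.

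**Working it through.** **Inputs from Sample size calculation:** two-sided α = 0.05; 90% power; SDs of change 1 and 3; difference in change 2; 27 evaluable and 33 enrolled per group; 99 in total.

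**Not in the documents, so assumed:** r, the correlation between baseline and month-1 ECWM, shown over a range; and the same SD, s, at both times.

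**1. The plan's own figure.** n = (1.96 + 1.28)² × (1² + 3²) / 2² = 10.4976 × 10 / 4 = 26.24, rounded up to 27. Then 26.24 / 0.8 = 32.8, rounded up to 33, and 3 × 33 = 99. The stated size reproduces. With average variance (1 + 9) / 2 = 5, 27 per group gives 90.8% power for a two-arm comparison of change.

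**2. Variance of three analyses of the same data.**

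- End value: s²
- Change: 2s²(1 − r)
- ANCOVA (month-1 value adjusted for baseline): s²(1 − r²)

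Hence ANCOVA relative to end value is 1 − r², and ANCOVA relative to change is (1 − r²) / [2(1 − r)] = (1 + r) / 2.

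| r | ANCOVA / end value | ANCOVA / change |
|---|---|---|
| 0.3 | 0.91 | 0.65 |
| 0.5 | 0.75 | 0.75 |
| 0.7 | 0.51 | 0.85 |

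These are large-sample ratios. With 3 × 27 = 81 evaluable participants, the covariate costs one of 81 − 3 = 78 residual degrees of freedom, which is negligible.

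**3. What this does to power.** Take the planning variance of 5 as the variance of change, as the protocol labels it. Then s² = 5 / [2(1 − r)]; for r = 0.7, s² = 5 / 0.6 = 8.33, and the ANCOVA variance is 8.33 × 0.51 = 4.25.

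| r | n per arm for 90%: end value / change / ANCOVA | Power with 27 per arm: end value / change / ANCOVA |
|---|---|---|
| 0.3 | 19 / 27 / 18 | 97.3% / 90.8% / 98.3% |
| 0.5 | 27 / 27 / 20 | 90.8% / 90.8% / 96.7% |
| 0.6 | 33 / 27 / 22 | 83.6% / 90.8% / 95.7% |
| 0.7 | 44 / 27 / 23 | 72.1% / 90.8% / 94.6% |
| 0.8 | 66 / 27 / 24 | 54.7% / 90.8% / 93.4% |

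End-value analysis keeps the stated power up to r of about 0.5 and loses it beyond that. Change holds 90.8% throughout. ANCOVA beats both in every row.

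**4. A limit of this set-up.** One common s and r cannot by itself produce change SDs of 1 in one arm and 3 in the other. The figures use the average variance, as the protocol's formula in effect does, so they show the pattern rather than forecast exact power.

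**The case against.** The strongest reply is that an unadjusted ANOVA is valid in a randomised trial. That stands: the estimate is unbiased on average, its standard error already allows for chance imbalance, and the type I error rate is not inflated by it. Nor is a loss of power certain, since with r at or below 0.5 even the end-value analysis meets the 90% target.

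It can also be said that covariates belong in an analysis plan that is not shown. The protocol does not leave the method open, however. It names a test and a fallback, and neither takes a covariate.

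Four stronger readings are tempting and are not supported.

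- **That the analysis contradicts the sample size.** The Primary outcome wording may mean change, the abstract speaks of evaluation before and after therapy, and the ANOVA sentence is garbled. This is an ambiguity, not a proven mismatch. If change is meant, the power shortfall disappears, but the (1 + r) / 2 loss against ANCOVA remains.
- **That baseline is to be tested for significance.** The sentence on baseline sits among descriptive statements and names no test or P value.
- **That time since onset is a neglected prognostic factor by the protocol's own account.** The Background says of Bell's palsy patients in general that "the majority of them will recover within 1–3 months". It does not say this of persistent hypophasis, which it describes as unchanging without suitable therapy.
- **That chance baseline imbalance passes whole into the result.** With 27 per arm its SD is √(2/27) = 0.27 baseline SDs. It reaches an end-value estimate only multiplied by the baseline slope, which is r under equal SDs: 0.08, 0.14 and 0.19 SDs at r = 0.3, 0.5 and 0.7. The protocol gives no baseline SD with which to turn these into millimetres.

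**Conclusion.** The point holds as one of precision and clarity. The primary test as written is valid on average but ignores a covariate that is already collected, and three sections do not agree clearly on what is compared.

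Under equal SDs, and over r = 0.3 to 0.7, adjustment removes 9% to 49% of the variance of an end-value ANOVA, or 35% to 15% of that of a change-score ANOVA. The gain is there on either reading of the outcome; its size depends on r, which the protocol does not give.

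A shortfall against the stated power is conditional. It arises only if end values are analysed, the planning variance is that of change, and r exceeds about 0.5; at r = 0.7 power is then about 72%. The change should be made, but the trial is not invalid without it.

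**What to change.** - State month-1 ECWM as the analysed quantity. Say which value counts for participants whose end-time measurement is taken at early recovery, as Study setting allows.
- Make the primary analysis a linear model of that value on group, with baseline ECWM as covariate and heteroscedasticity-robust standard errors. The planned change SDs of 1 and 3 make a common variance doubtful, and eye crack width has a floor at zero.
- Report the adjusted A–B and A–C differences with 95% CIs.
- Keep a rank-based or ordinal analysis as a sensitivity analysis instead of a fallback that replaces the primary one.
- Adjust ESA for baseline ESA in the same way. Because ESA is graded 0 to 5, an ordinal sensitivity analysis matters most there.
- Align the wording of Primary outcome, Sample size calculation and Statistical analysis. The planned 27 per arm can stand: under the assumptions above it gives ANCOVA more than 90% power at every r shown.

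The cost is a documented wording change before data lock. No new data, visits or participants are needed. The downside is small: slightly more modelling, and one more assumption, a linear relation with baseline. Whether the named SPSS version provides the robust standard errors should be confirmed.

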## Methods/design

### Objective

The present study assessed the augmenting effect of acupuncture therapy on the acu-point Bi’nao for hypophasis through eye crack width and eyelid strength compared to a sham acu-point and no acupuncture treatment on Bi’nao.

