### Randomization and blinding

Figure 2 illustrates the schedule of enrolment, allocation, interventions, and assessments in this trial. The enrolled participants will be randomly assigned to group A, B, or C (1:1:1). An independent statistician will generate the block randomization scheme in a blinded manner. The table will be managed by another independent researcher who is not involved in the recruitment, acupuncture treatment, or assessment. The CRC will send the assignment information to the researcher who will conduct the random allocation; subsequently, the researcher will only provide assignment information to the doctors of TCM, who will perform the acupuncture treatment. In order to ensure concealing of the allocation, the information will be recorded in an allocation log by the researcher and not opened until the data are locked. The participants will be blinded to the type of acupuncture treatment; the assessor, data managers, statisticians, and study monitors will be blinded to the allocation. The blinding will be maintained until the data are locked. For evaluation in a blinded manner, the allocation guessing will be assessed immediately after the final treatment. The practitioners and assessors will be instructed to treat the participants according to the predefined standard operating procedures (SOPs) during the trial to maintain blinding; un-blinding will be considered only in the case of rights and safety of the participants, including the occurrence of serious adverse effects (SAEs). In such cases, the researchers will notify the principal investigator (PI) and document the subsequent processes.

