### Outcome measures

#### Primary outcome

ECWM will be performed using a graduated ruler to measure the width (mm) between the upper and lower eyelids when the patients attempt to close his eyes. The measurements will be taken three times and the average recorded. ECWM will be performed before acupuncture therapy as the primary time measurement, weekly during the treatment duration, and at the first month after the first therapy by three physicians, and the average value recorded. The mean value and standard deviation among the participants in every group will be calculated; the differential values of eye crack width (mm) between the intervention and control groups will be compared.

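### The stated primary test is a three-group omnibus ANOVA, but the objective and the 90% power both concern two-group comparisons, and the powered one does not identify its control arm

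*Protocol article*

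**What the plan says.** All references are to the protocol article. Patients are allocated 1:1:1 to basic acupuncture plus Bi'nao (A), basic acupuncture plus a point 1 cm away (B), or basic acupuncture alone (C).

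- **Objective:** the effect of Bi'nao is to be judged "compared to a sham acu-point and no acupuncture treatment on" Bi'nao. That is two comparators. The Background gives the purpose of the trial as a comparison with a placebo point.
- **Primary outcome:** "the differential values of eye crack width (mm) between the intervention and control groups will be compared". Two arms could be the control here.
- **Sample size calculation:** a "two-sided superiority test, where α = 0.05, power = 90"%. The SD of the change in eye crack width (ECWM) "in the control group was presumed as 1 point and that in the treatment group as 3 points". The relevant effect is a change that "in the treatment group is 2 points higher than that in the control group". Only two groups appear, and the control group is not identified as B or C.
- **Statistical analysis:** for the primary and secondary outcomes, "one-way ANOVA test will be applied to identify the differences between the of ECWM values and ESA scores among the groups". Kruskal–Wallis replaces it for non-normal data. The threshold is a two-sided P < 0.05. No pairwise contrast or order of testing is given.

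**The concern.** Three sections describe three different hypotheses. The objective needs A against B and A against C. The sample size covers one unnamed pair. The test examines whether any of the three means differ.

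The omnibus hypothesis fails whenever at least one arm differs from another, for any reason. A and B share something that C lacks: an additional needle in the upper arm, three times a week. If that needle has some effect wherever it is placed, the F test can be significant although Bi'nao is no better than the point 1 cm away. The Discussion itself allows that needling may cause non-specific physiological reactions. What is at stake is whether a significant primary result answers the question about Bi'nao, and whether the reader knows which comparison has 90% power.

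**Working it through.** **Inputs from the article.** Two-sided α 0.05 (z = 1.96), power 90% (z = 1.28), SDs of change 3 (treatment) and 1 (control), difference 2, three equal arms, 20% dropout. The sample size section counts in points and the outcome is in millimetres; I read one point as 1 mm.

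**Inputs that I had to assume.** Normal data, and a mean effect and SD for the sham arm. The article gives neither, so ranges are shown.

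**1. The plan's own figure.** n = (1.96 + 1.28)² × (1² + 3²) / 2² = 10.4976 × 10 / 4 = 26.24, taken as 27 per arm. For dropout, 26.24 / 0.8 = 32.8, taken as 33, and 3 × 33 = 99. The figure reproduces as one two-group, two-sided comparison.

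**2. What the F test can distinguish.** Take a common SD of √5, whose variance is the mean of 3² and 1². The noncentrality parameter is λ = n × Σ(μᵢ − μ̄)² / 5.

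- Only A better by 2, means (2, 0, 0): Σ = (4/3)² + 2 × (2/3)² = 2.667.
- A and B equally better by 2, means (2, 2, 0): Σ = 2 × (2/3)² + (4/3)² = 2.667.

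At 27 per arm, λ = 27 × 2.667 / 5 = 14.4 in both cases and the power of F is 92.5% in both. The F test gives the same answer whether the effect is entirely specific to Bi'nao or not specific at all.

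**3. No point-specific effect, by size of the shared effect.** Simulation with A = B, SDs 3/3/1 and 26–27 per arm:

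| Shared effect of A and B over C | F significant |
|---|---|
| 0.5 mm | about 10% |
| 1 mm | 28–29% |
| 2 mm | 90–91% |

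A versus B by Welch test is significant in about 5% of these trials, as it should be.

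**4. Power of A versus B at a true difference of 2 mm.** The normal approximation is Φ(2 / √((σ_A² + σ_B²)/n) − 1.96). With σ_A = 3, σ_B = 1 and n = 27: 2 / √(10/27) = 3.286, and Φ(1.326) = 90.8%. The Welch test, by simulation, gives:

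| Sham-arm SD | 27 per arm | 33 per arm (no dropout) |
|---|---|---|
| 1 | about 89% | about 94% |
| 3 | about 67% | about 76% |

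The stated 90% therefore fits A versus B only if the sham arm varies like the planned control group.

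**The case against.** The strongest reply is that this is a condensed article and that pairwise follow-up may stand in an analysis plan that is not shown. The statistical section does not call the F test the success criterion and does not rule out contrasts. The Background and the primary outcome section both point towards a comparison with a control. This stands in part. A reader might infer that the trial would be declared positive on F alone, but the article does not say so. What remains is that the article does state the test for the primary outcome, and that test matches neither its objective nor its sample size basis. The wording about intervention and control groups cannot settle the matter when there are two control arms.

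Second, the 2 mm row is an extreme. It gives the sham needle the whole effect that the plan calls clinically significant, while the Discussion expects sham needling to act only lightly. That is fair, and it is why the range is shown: at 0.5 mm the figure is about 10%.

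Third, a reader might infer that group C patients cannot be blinded and that only A versus B is a blinded comparison. The article does not establish this. It says that participants are blinded to the type of acupuncture, and all are told that they will receive acupuncture. The per-session count is 8–9 needles, and nothing says that C patients learn of an arm needle. The case here does not depend on blinding.

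Fourth, a reader might conclude that the trial is underpowered because A must beat both controls. No section sets that requirement. If it were set, with SDs 3/1/1, joint success would be 84–86% at 26–27 per arm and about 92% at 33. The omnibus test itself has 92–93% power at 26–27 in that scenario.

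Finally, with three groups, pairwise tests after a significant F also control the family-wise error when variances are equal. This is a legitimate alternative in general, but the plan itself assumes SDs of 3 and 1. With SDs 3/1/1 and no true difference, the equal-variance F rejects in about 7% of simulated trials.

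**Conclusion.** The point holds as a mismatch between what the article asks, what it sizes and what it tests. A significant omnibus result would not show that Bi'nao differs from the sham point. How often that would mislead depends on the non-specific effect of an extra needle: about 10% to 91% of trials for shared effects of 0.5 to 2 mm, assuming normal data and SDs of 3/3/1. None of the sham-arm values comes from the article.

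The sample size arithmetic is sound for one pair. The finding is not that the omnibus test lacks power, nor that 90% is miscalculated. It is that the comparison to which 90% applies is not identified, and that for A versus B the power could be about 89% or about 67% at 27 per arm, depending on an unstated SD. This should be fixed before the data are unblinded.

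**What to change.** In the statistical analysis section:

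1. Name A versus B on the change in ECWM as the primary test, two-sided at 0.05, with an unequal-variance method such as Welch's test. This contrast isolates the point-specific effect.
2. Test A versus C at two-sided 0.05 only if A versus B is significant. The fixed order keeps the family-wise error at 5% without splitting α.
3. Report the omnibus F test as supportive.

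In the sample size section, say which arm is the control group, state the SD assumed for the sham arm, and restate the A-versus-B power to match. It should not simply declare that 90% refers to A versus B: the Welch figure at 27 per arm is about 89% with a sham SD of 1 and about 67% with a sham SD of 3 (about 94% and 76% if all 33 are evaluable).

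The cost is wording, with N = 99 unchanged. There are two downsides. A versus C cannot be claimed as confirmatory if A versus B fails. The stated power may also become less favourable: with a sham SD of 3, the plan's own formula gives 10.4976 × (9 + 9) / 4 = 47.2, or 48 evaluable per arm for 90%. The sponsor would then have to accept the lower power openly or reconsider the number.
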